### 2.11. Statistical Analysis

Three datasets will be used for statistical analysis, including a full-analysis set (FAS), per-protocol analysis set (PPS), and safety analysis set (SS). The FAS is the dataset composed of participants who have at least one postmedication evaluation data. The last observation carried forward (LOCF) method will be used for the missing data supplement. The PPS is the dataset composed of participants who meet the inclusion criteria, show good compliance, and complete the treatment plan. The SS is the dataset of all participants randomized to study, and safety record will be assessed, including adverse events and laboratory test results. All statistical tests are two-sided tests, and *P* < 0.05 will be considered statistically significant. Enumeration data will be expressed as frequency and analyzed using the chi-square test or Wilcoxon rank sum test. Measurement data will be described by means, standard deviation, maximum value, and minimum value and compared between groups using the group *t*-test, Fisher's exact test, or Wilcoxon rank sum test. Statistical analysis will be completed by the third-party statisticians.

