### 2.6. Outcome Measurement

#### 2.6.1. Indexes of End Point

Incident diabetes according to the guideline for the prevention and treatment of type 2 diabetes (2017 edition)Normalization of Blood Glucose, FPG <5.6 mmol/L or 2h PBG <7.8 mmol/L

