### 2.7. Study Visits and Data Collection

The study is divided into two periods, a 24-week drug intervention period and a 24-month follow-up period. After the intervention period commences, telephone visits will take place every 2 weeks and outpatient visits every 4 weeks. When the follow-up period commences, outpatient visits will take place every 6 months. An overview of data capture can be found listed in Table 1.

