### 2.10. Sample Size Calculation

According to previously published research [11], the annual conversion rate of IGT into T2DM was 1.5% in the TCM group and 10% in the control group. We predicted that the annual conversion rate of IGT into T2DM was 5.7% in the TCM comprehensive intervention group. Therefore, assuming that *α* = 0.05 and *β* = 0.1 according to the one-sided test, u*α* = 1.645 and u*β* = 1.282, and the data will be placed in the formula to obtain *n* = 299.94. Therefore, each group needs more than 300 participants, for a total of 600 participants.

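### Unrestricted LOCF over 30 months, with only frequency tests named for incident diabetes, understates incidence and biases the comparison when loss is unequal or outcome-related

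*Protocol article*

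**What the plan says.** Section 2.11 sets the missing-data rule in one sentence: "The last observation carried forward (LOCF) method will be used for the missing data supplement". It does not say which endpoint or which period the rule covers. For categorical results the same section says: "Enumeration data will be expressed as frequency and analyzed using the chi-square test or Wilcoxon rank sum test". It names no method that uses time at risk or censoring, and no second missing-data analysis. The full-analysis set is defined by "The FAS is the dataset composed of participants who have at least one postmedication evaluation data".

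Section 2.6.1 lists as an end point "Incident diabetes according to the guideline for the prevention and treatment of type 2 diabetes (2017 edition", together with normalization of blood glucose. Section 2.6.2 names changes in FBG, 2h PBG and HbA1c as the primary outcome. Section 2.10 sizes the study on the annual rate of conversion to diabetes.

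On duration, Section 2.7 says: "The study is divided into two periods, a 24-week drug intervention period and a 24-month follow-up period". It adds: "When the follow-up period commences, outpatient visits will take place every 6 months". Table 1 places the last visit at month 30.

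Two sections govern leaving the study. Section 2.4.5 scores withdrawal for a marked glucose rise, or for severe or frequent hypoglycemia, as a treatment failure. Section 2.4.6 lists loss of contact, poor clinical efficacy, adverse reactions, cost and moving away, with no scoring rule.

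**The concern.** Incident diabetes accrues with time. If someone is last seen free of diabetes at week 24 and never returns, LOCF records that person as free of diabetes two years later, and the person stays in the denominator as a success. The more people an arm loses, the lower its apparent incidence.

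The same rule reaches the primary outcome. Someone lost between week 24 and month 12 has an on-treatment glucose or HbA1c value carried past the end of treatment, up to month 30.

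Unequal loss is plausible here. Participants choose their own group. The Section 2.4.5 removal rules for study-drug allergy, drug-related adverse findings and drug compliance can in practice apply only to the TCPM arm. The Discussion itself expects the long treatment and follow-up to strain compliance. Outcome-related loss is plausible too, since Section 2.4.6 includes withdrawal for poor efficacy.

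**Working it through.** **Inputs from the protocol.** Annual conversion is 10% in controls (Section 2.10: "the annual conversion rate of IGT into T2DM was 1.5% in the TCM group and 10% in the control group") and 5.7% planned for the intervention ("We predicted that the annual conversion rate of IGT into T2DM was 5.7% in the TCM comprehensive intervention group"). There are 300 participants per group. Tests are two-sided at 5%, so 2.5% in each direction. Follow-up is 30 months (Section 2.7, Table 1).

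**Assumptions.** The document gives no loss rate, so every loss rate below is assumed. Conversion runs at a constant rate, and loss is unrelated to outcome. The plan has no figure of its own for loss or 30-month risk to reproduce. Its sample-size figure is not used here except for the 300 per group.

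**Step 1: true risks.**
- Control, 30 months: 1 − 0.9^2.5 = 0.2316. By week 24: 1 − 0.9^(24/52) = 0.0475.
- Intervention as planned, 30 months: 1 − 0.943^2.5 = 0.1365. By week 24: 1 − 0.943^(24/52) = 0.0267.

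**Step 2: risk that LOCF shows.** If a fraction L is lost just after week 24, people already diagnosed keep their diagnosis and the rest are carried as diabetes-free:

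LOCF risk = (1 − L) × 30-month risk + L × week-24 risk

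**Step 3: no true effect, 10% a year in both arms.**
- L = 0.15: 0.85 × 0.2316 + 0.15 × 0.0475 = 0.204
- L = 0.25: 0.75 × 0.2316 + 0.25 × 0.0475 = 0.186
- L = 0.30: 0.70 × 0.2316 + 0.30 × 0.0475 = 0.176

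The standard error of the difference is √(2p̄(1 − p̄)/300), about 0.0323 for the first pair and 0.0320 for the second. The differences of 0.0184 and 0.0276 shift the test statistic by 0.57 and 0.86. The chance of a significant result in the favoured direction is then P(Z > 1.96 − shift).

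| Loss TCPM / control | LOCF risk TCPM / control | Risk ratio | False positive in the favoured direction (nominal 2.5%) |
|---|---|---|---|
| 20% / 20% | 19.5% / 19.5% | 1.00 | 2.5% |
| 25% / 15% | 18.6% / 20.4% | 0.91 | 8.2%, for TCPM |
| 30% / 15% | 17.6% / 20.4% | 0.86 | 13.6%, for TCPM |
| 15% / 25% | 20.4% / 18.6% | 1.10 | 8.2%, for control |

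**Step 4: planned effect, 20% lost in each arm.** Control: 0.8 × 0.2316 + 0.2 × 0.0475 = 0.195. Intervention: 0.8 × 0.1365 + 0.2 × 0.0267 = 0.1145. The difference falls from 9.5 to 8.0 points, while the risk ratio stays at 0.59.

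**Step 5: gradual loss.** Let D be the fraction lost by month 30, μ = −ln(1 − D)/30 the monthly loss rate, v₁, v₂, … the Table 1 visits in months with v₀ = 0, and S(t) = 0.9^(t/12). Diabetes is found at the next attended visit, so the LOCF risk in the full-analysis set is Σ[S(vₖ₋₁) − S(vₖ)]·exp(−μvₖ) / exp(−μv₁). With no true effect:
- 25% / 15% loss: 19.9% vs 21.3%, risk ratio 0.94, about 5.9% false positives for TCPM.
- 30% / 15% loss: 19.3% vs 21.3%, risk ratio 0.91, about 8.8%.
- 30% / 10% loss: 19.3% vs 21.9%, risk ratio 0.88, 12.5% two-sided rejection against a nominal 5%.
- 40% / 10% loss: 17.9% vs 21.9%, risk ratio 0.82, 23.5% two-sided rejection.

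In 3,000 simulated trials of each of the last two cases, a log-rank test censoring at the last visit rejected 4.8% and 5.3% of the time.

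**The case against.** **The plan is condensed.** An article may leave the survival method to an analysis plan that is not shown. Section 2.11 never names incident diabetes, so its test is inferred from a general rule for frequencies. This stands as a limit on certainty. The LOCF sentence, however, is a positive and unrestricted choice, and none of the listed tests handles censoring.

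**A reader might infer that everyone lost is counted as diabetes-free.** The document does not support that. People diagnosed before loss keep their diagnosis. Section 2.4.5 scores withdrawal for a marked glucose rise as a failure. People with no post-medication evaluation leave the full-analysis set.

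**A reader might infer that long-term glucose is frozen at its best value.** Nothing says that week 24 is the best value, and someone lost after month 18 carries the month-18 value.

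**A reader might infer that the bias must favour TCPM.** It follows whichever arm loses more. The drug-related removal rules point to the TCPM arm during treatment, but participants chose their group, and controls could equally leave more often during follow-up.

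**A reader might infer that chi-square is itself an error.** All participants have the same planned follow-up, so comparing 30-month proportions is valid when follow-up is complete or comparable. The fault lies in pairing it with LOCF.

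**Placing all losses at week 24 is severe.** That stands. Step 5 shows smaller bias at the same loss rates when loss is gradual.

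**Conclusion.** The point holds for participants lost before diagnosis, other than the Section 2.4.5 withdrawals scored as failures and those outside the full-analysis set. LOCF to month 30 understates incidence. It also turns unequal loss into an apparent treatment difference, of benefit or of harm.

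With a 10 to 15 point imbalance and no true effect, the risk ratio moves to 0.91 to 0.86 if all loss falls at week 24, and to 0.94 to 0.91 if loss is gradual. False positives for TCPM rise from 2.5% to between about 5.9% and 13.6%. Equal loss unrelated to outcome leaves the test valid but shrinks the difference and costs power.

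Confidence is high in the mechanism. The size rests wholly on assumed loss rates and on conversion at the plan's 10% a year. The figures concern incident diabetes. For the primary glucose and HbA1c outcomes the fault is the same in kind but is not quantified here. The plan should be changed before outcome data are analysed.

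**What to change.** Replace the LOCF sentence in Section 2.11 and name the analysis for each endpoint:

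- **Incident diabetes:** time to diagnosis over 30 months, censored at the last glucose assessment, using a discrete-time (grouped) proportional hazards model at the scheduled visits.
- **FBG, 2h PBG and HbA1c:** a mixed model for repeated measures with baseline, group, visit and group-by-visit terms.
- **Sensitivity analyses:** LOCF, beside an analysis in which those lost are assumed to do worse. The second is needed because Section 2.4.6 includes withdrawal for poor efficacy, and censoring alone does not remove that bias.

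**Cost.** Table 1 already schedules the measurements, so the change needs revised wording and some extra programming. Both main analyses assume data missing at random, or censoring unrelated to outcome, and that assumption must be probed. The sample-size text should be restated to match a time-to-event comparison. At the plan's rates with 300 per group, simulated power is 86% for both log-rank and chi-square with no loss, and 81% against 80% with 20% gradual loss in each arm. The change therefore costs no power.

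### The sample size assumes a one-sided 5% test, but the analysis is two-sided at 5%, so the stated 90% power is not the power of the planned test

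*Protocol article*

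**What the plan says.** Section 2.10 (Sample Size Calculation) sets α = 0.05 and β = 0.1 "according to the one-sided test" and prints the two normal quantiles, 1.645 and 1.282. Its event rates are an annual conversion of "10% in the control group" and the prediction that "the annual conversion rate of IGT into T2DM was 5.7% in the TCM comprehensive intervention group". The result is 299.94, from which the article takes 300 per group and 600 in total.

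Section 2.11 (Statistical Analysis) says "All statistical tests are two-sided tests" and sets significance at P below 0.05. For counts, such as the number converting to diabetes, it says: "Enumeration data will be expressed as frequency and analyzed using the chi-square test or Wilcoxon rank sum test". It makes no exception for the conversion comparison, and no other section declares a one-sided hypothesis.

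**The concern.** The two sections describe different tests. One-sided 0.05 rejects beyond 1.645 in one direction. Two-sided 0.05 rejects beyond 1.96 in either direction, so in the direction that favours the patent medicines it spends only 0.025. This is not a difference of notation, because the one-sided counterpart of a two-sided 0.05 test is one-sided 0.025.

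At stake is the stated power. The 600 participants are justified by a 10% chance of missing the assumed effect, and that chance was worked out for a test that section 2.11 does not allow. The point concerns the conversion comparison only. The primary outcome in section 2.6.2 (changes in fasting glucose, 2-hour glucose and HbA1c) is not covered by the calculation in section 2.10.

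**Working it through.** **Inputs.** From section 2.10: critical value 1.645 (one-sided 0.05), 1.282 (power 90%), 10% against 5.7% per year, n = 299.94. From section 2.11: two-sided 0.05, hence 1.960. From section 2.5: 1:1 allocation.

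**Step 1. The plan's own figure.** Per group, with pooled variance under the null:

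n = [z_α √(2 p̄(1 − p̄)) + z_β √(p₁(1 − p₁) + p₂(1 − p₂))]² / (p₁ − p₂)²

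With p₁ = 0.10, p₂ = 0.057 and p̄ = 0.0785, the two roots are √0.144676 = 0.38036 and √0.143751 = 0.37915, and (p₁ − p₂)² = 0.001849.

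- One-sided: (1.645 × 0.38036 + 1.282 × 0.37915)² / 0.001849 = 668.5, so 669 per group.
- Two-sided: (1.960 × 0.38036 + 1.282 × 0.37915)² / 0.001849 = 820.3, so 821 per group.

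The printed 299.94 is not reproduced. Other one-sided versions give 714 (continuity correction), 666 (unpooled) and 658 (arcsine). A figure near 299.94 appears if both annual rates are doubled to 2-year risks, 20% against 11.4%: about 302 unpooled or 305 pooled. The article does not state that step.

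**Step 2. The effect of sidedness alone.** This does not need the rates. If n gives 90% power with 1.645, the standardised effect is 1.645 + 1.282 = 2.927. Against 1.960:

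- Power = Φ(2.927 − 1.960) = Φ(0.967) = 83.3%.
- Ratio of sizes for 90% power = ((1.960 + 1.282) / (1.645 + 1.282))² = (3.242 / 2.927)² = 1.227.
- 299.94 × 1.227 ≈ 368 per group, or 736 in total.

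The exact formula agrees on the printed rates: 820.3 / 668.5 = 1.227.

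**Step 3. Power at 300 per group.** The article gives no horizon, so every row except the first is an assumption. All rows assume complete outcomes on 300 per group and an unadjusted comparison of two proportions.

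| Rates used | Control vs intervention | One-sided 0.05 | Two-sided 0.05 |
|---|---|---|---|
| Annual, as printed | 10% vs 5.7% | 62.3% | 49.9% |
| 2 years, compounded | 19.0% vs 11.1% | 85.9% | 77.6% |
| 2 years, doubled | 20% vs 11.4% | 89.6% | 82.7% |
| 30 months, compounded | 23.2% vs 13.6% | 91.5% | 85.4% |
| 30 months, linear | 25% vs 14.25% | 95.4% | 91.4% |

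Compounded means 1 − (1 − r)^t: for example 1 − 0.90^2.5 = 0.232 and 1 − 0.943^2.5 = 0.136. Linear means r × t.

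**Step 4. Separating the two defects.** On the printed rates, 300 per group gives 62.3% even with the one-sided test. Of the gap from 90% to 49.9%, the part from 90% to 62.3% (27.7 points) comes from 299.94 not following from those rates. Sidedness accounts for the remaining 12.4 points at that size. On a size that truly has 90% power one-sided, sidedness costs about 7 points.

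**The case against.** The best defence has three parts.

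First, the loss is modest. Power of 83% is still above 80%, and neither the test nor the data change. This stands, and it limits the size of the point. It does not reconcile the two sections.

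Second, power may not fall short of 90% at all. If conversion is counted over 30 months with linearly scaled rates, 300 per group gives 91.4% two-sided. This also stands, so it cannot be said that two-sided power is below 90% on every horizon. But the article names no such horizon, and those rates would have needed only 232 per group one-sided, not 299.94. On every set of rates the two-sided power is lower than the one-sided power that section 2.10 claims.

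Third, one-sided planning can be legitimate. It can, if the analysis matches it, and here section 2.11 rules that out.

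Two stronger readings are tempting. A reader might infer that the mismatch leaves room to claim success on a one-sided p-value, doubling the false-positive risk in favour of the medicines. The document does not support this: section 2.11 makes every test two-sided, and the sidedness in section 2.10 is a planning assumption that authorises no analysis. A reader might also attribute the 50% power on annual rates to sidedness. Step 4 shows that most of that shortfall is the separate problem with the event rates.

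**Conclusion.** The inconsistency is real and explicit. The stated 90% power for the conversion comparison does not belong to the two-sided test that section 2.11 prescribes. On sidedness alone it is about 83%, or equivalently 90% would need about 368 per group in place of 299.94. Both figures take the article's 299.94 as valid for 90% one-sided power, and use only the normal quantiles.

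The power that 300 per group actually gives cannot be fixed from the article, because the time horizon is not stated. It ranges from about 50% on the printed annual rates to about 91% on linear 30-month rates. The failure of 299.94 to follow from the annual rates is a separate and larger defect, and correcting it would leave the conflict between the two sections in place. The finding does not show an inflated false-positive rate, and it does not by itself require a larger study.

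**What to change.** Keep the two-sided 0.05 test of section 2.11. In section 2.10, replace the one-sided wording and 1.645 with two-sided and 1.96. Then restate the power that 300 per group gives for the conversion comparison, naming the formula, the event rates in each group and the time horizon over which conversion is counted. The horizon has to be settled first, since the restated figure depends on it: on sidedness alone about 83% in place of 90%, and otherwise as in the table under the working.

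The cost is a change of wording and, on most readings, a less favourable stated power. No more patients are needed and no analysis changes.

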## 2. Methods

### 2.1. Trial Design

This study is a multicenter cohort study with two arms. A total of 600 participants will be recruited. The participants will be divided into either intervention or control groups according to their own desire, and the exposure factor is the application of TCPMs. All participants will be encouraged to lead a healthy lifestyle, and the intervention group also used TCPMs based on syndrome differentiation. Incident diabetes and normalization of blood glucose are indexes of end point. Safety assessments and adverse event monitoring will also be conducted. The treatment duration is set for 24 weeks, and we will follow-up for another 2 years.

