### 2.3. Study Population and Recruitment

A total of 600 participants will be recruited from six hospitals in mainland China, including Guang'anmen Hospital of the China Academy of Chinese Medical Sciences, Beijing Shijitan Hospital, Capital Medical University, Beijing Changping District Hospital of Chinese Medicine, Beijing Shunyi District Hospital of Chinese Medicine, Beijing Miyun District Hospital of Chinese Medicine, and Beijing Pinggu District Hospital of Chinese Medicine. The participants will be divided into either the intervention group or the control group (1 : 1). Participants should be included according to the diagnostic criteria and inclusion criteria and should be refused according to the exclusion criteria. Eligibility criteria are listed as follows.

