#### 2.6.2. Primary Outcome

The primary outcome is the changes of fasting plasma glucose (FBG), two-hour postprandial blood glucose (2h PBG), and glycosylated hemoglobin (HbA1c). Blood glucose is evaluated every 4 weeks, and HbA1c is evaluated every 12 weeks.

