## 3. Discussion

In the present clinical practice in China, prevention of T2DM mainly depends on the improvements in unhealthy lifestyles, which is hard to persist in. Several large-scale trials have demonstrated that use of some hypoglycemic drugs can decrease the incidence of diabetes to various degrees in those with prediabetes [12–15], though none are approved by the U.S. Food and Drug Administration, specifically for diabetes prevention. The cost, adverse reactions, tolerance, and other factors are also needed to be considered [4, 16]. TCM may hold a promise in the prevention of T2DM because of its characteristics of “treat disease before it arises,” which include strengthening the body constitution and regulating the high-risk factors leading to diabetes; in addition, TCM could also control the development of T2DM. This cognition corresponds with the thought of the prevention of T2DM. Prediabetes may fall under the TCM patterns of “spleen pyretic abundance,” etc. [17]. The main pathogenesis lies in spleen and stomach congestion, dampness-heat accumulation in the spleen, spleen deficiency and phlegm obstruction, liver depression and qi stagnation, and qi-yin dual insufficiency [9, 10]. In China, many prediabetic patients are more likely to choose the complementary TCPMs. Postmarketing TCPMs possess steady drug composition and defined dosage, which is convenient to observe the efficacy. In recent years, some randomized controlled trials (RCTs) have proved that TCPMs alone or TCPMs combined with lifestyle modification could be an effective intervention for the preventative treatment of T2DM [18–20]. Now, we aim to implement a clinical trial to observe the efficacy of TCPMs in the prevention of T2DM in Chinese subjects. The strength of our trial is that the trial design is a prospective cohort study, not an RCT, and the choice of intervention drugs in our trials is based on syndrome differentiation and treatment, which are more in accord with the clinical practice of TCM. The treatment duration is 6 months, and follow-up is continued for another two years, which is to observe the short-term and long-term effects of TCPMs. As to outcome assessment, we emphasize for incident diabetes and normalization of blood glucose, improvement of symptoms is also important for prediabetic patients to increase the quality of life.

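### Participants choose their own group, but the plan names only unadjusted between-group tests, so the treatment comparison is open to confounding of unknown size and direction

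*Protocol article*

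**What the plan says.** **Allocation.** Section 2.1 states: "The participants will be divided into either intervention or control groups according to their own desire". Section 2.3 adds a ratio: "The participants will be divided into either the intervention group or the control group (1 : 1"). The Discussion presents the non-randomised design as an advantage: "The strength of our trial is that the trial design is a prospective cohort study, not an RCT".

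**Outcomes.** Section 2.6.2 states: "The primary outcome is the changes of fasting plasma glucose (FBG), two-hour postprandial blood glucose (2h PBG), and glycosylated hemoglobin (HbA1c"). Section 2.6.1 lists incident diabetes and normalization of blood glucose as the end-point indexes.

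**Comparison methods.** Section 2.11 names them for both data types. Categorical: "Enumeration data will be expressed as frequency and analyzed using the chi-square test or Wilcoxon rank sum test". For continuous data the choices are the t-test, Fisher's exact test or the rank sum test, in a sentence that begins: "Measurement data will be described by means, standard deviation, maximum value, and minimum value and compared between groups using the group". The article mentions no regression, matching, stratification, propensity score or centre term.

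**Analysis sets.** Section 2.11 defines the safety set thus: "The SS is the dataset of all participants randomized to study". It defines the full-analysis set thus: "The FAS is the dataset composed of participants who have at least one postmedication evaluation data".

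**Limitations.** The Discussion lists the lack of a placebo and possible poor compliance. It names neither self-selection nor confounding.

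**The concern.** The abstract promises evidence on the efficacy of TCPMs plus lifestyle intervention against lifestyle intervention alone, which is a causal claim. People who choose to take a medicine three times a day for 24 weeks may differ from those who decline in motivation, glycaemia, BMI, TCM syndrome or hospital. In a study where both groups are asked to change diet and exercise, motivation is itself likely to predict outcome. The 1:1 ratio balances numbers, not prognosis.

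An unadjusted test compares the groups as they formed. The result mixes any TCPM effect with the characteristics of those who chose TCPM, and could show prevention that is absent or hide prevention that is present. A larger sample only narrows the interval around the mixed quantity.

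Two analysis-set definitions add a smaller difficulty of wording. Nobody is randomised, so the safety set has no members if read literally. Controls receive no study medicine, so the full-analysis set is unclear for them.

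**Working it through.** The plan gives no figure for confounding, so there is none to reproduce. The sample-size calculation in 2.10 is a separate matter, and nothing below depends on whether it is right.

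**Inputs from the protocol**
- Group size 300 and control conversion 10% per year (2.10).
- Last visit at 30 months (Table 1), so control risk = 1 − 0.90^2.5 = 23.2%.
- Two-sided tests at 0.05 (2.11), so 2.5% in the direction favouring TCPM.

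**Assumed inputs** (not in the protocol): the strength of a prognostic trait, its prevalence in each group, and the glucose slope, SD and baseline differences.

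**A. Incident diabetes, no true effect.** A protective trait with risk ratio rr is present in a share pT of the TCPM group and pC of controls.

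Spurious RR = [1 − pT(1 − rr)] / [1 − pC(1 − rr)]

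TCPM risk = 0.232 × spurious RR. The false-positive rate favouring TCPM is Φ{(difference − 1.96 × SE0)/SE1}, where SE0 is the pooled and SE1 the unpooled standard error at 300 per group.

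| Case | rr | pT vs pC | Spurious RR | Difference | SE0 / SE1 | False positive for TCPM (nominal 2.5%) |
|---|---|---|---|---|---|---|
| Weak | 0.8 | 55% vs 45% | 0.89/0.91 = 0.978 | 0.0051 | 0.0343 / 0.0343 | 3.5% |
| Moderate | 0.6 | 60% vs 40% | 0.76/0.84 = 0.905 | 0.0221 | 0.0339 / 0.0338 | 9.5% |
| Strong | 0.5 | 70% vs 30% | 0.65/0.85 = 0.765 | 0.0545 | 0.0329 / 0.0328 | 38% |

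At a control risk of 10% the moderate case falls to 5.9%. If the trait were commoner among controls, the same bias would run against TCPM.

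**B. Change in glucose, no true effect.** Assume that change depends on the baseline value with slope 0.4 (regression to the mean) and that the SD of change is 0.7 mmol/L. Then SE = 0.7 × √(2/300) = 0.0572.

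| Baseline difference (mmol/L) | Spurious difference in change | Shift / SE | Two-sided type I error (nominal 5%) |
|---|---|---|---|
| 0.05 | 0.05 × 0.4 = 0.02 | 0.35 | 6.4% |
| 0.1 | 0.04 | 0.70 | 11% |
| 0.2 | 0.08 | 1.40 | 29% |

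Taking changes removes part of a baseline glucose difference. The slope term above is what remains, and imbalance in BMI, hospital or motivation is untouched. For incident diabetes and normalization, taking changes does nothing.

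**C. Events available for adjustment.** At the rates in 2.10 (10% and 5.7% per year) over 2.5 years, the risks are 23.2% and 1 − 0.943^2.5 = 13.6%. Expected events = 300 × 0.2316 + 300 × 0.1365 ≈ 69.5 + 40.9 ≈ 110, before any dropout. A full covariate list (age, sex, BMI, three glycaemia values, four lipids, two blood pressures, four syndromes, concomitant medication, six hospitals) takes 1+1+1+3+4+2+3+1+5 = 21 parameters, or about 110/21 ≈ 5 events each. That is thin for direct adjustment.

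**D. Cost in precision.** If group choice correlates with the covariates at an assumed R² of 0.1 to 0.3, the required sample grows by 1/(1 − R²), a factor of 1.11 to 1.43.

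**The case against.** - **The analysis plan is not shown, and covariate lists usually belong there.** This stands for the list, which is only a suggestion here. It does not rescue 2.11, which names the comparison methods itself. They do not fit the allocation, and an adjusted analysis would depart from the published text.
- **A reader might infer that the estimate is biased, and in favour of TCPM.** The documents do not support that. There are no baseline data, shared eligibility criteria narrow the differences between groups, and the weak case above is close to harmless. What can be said is that the comparison is open to confounding and that the plan has no means of removing it.
- **A reader might infer that the study is planned throughout as though randomised.** That is too strong. The article repeatedly calls it a cohort study and says it is not an RCT. Only the safety-set definition uses the language of randomisation.
- **The primary outcome is a change, which already deals with baseline.** This is partly right, as B shows, but only for glycaemia and only in part.
- **The analysis-set wording is a side issue.** Agreed: the full-analysis-set term may be loose wording for post-baseline. These points need correcting but do not cause the confounding.
- **Adjustment cannot reach motivation.** This stands. The diet and activity diaries in 2.6.5 are kept during the intervention, hence after allocation, and no baseline measure of motivation is described.

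**Conclusion.** The concern holds as a mismatch between a self-selected design and the unadjusted tests the plan names. It affects the primary outcome and both end-point indexes, and should be corrected before data are examined, because covariates chosen afterwards invite selective adjustment.

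The size is unknown. Under the assumed scenarios the false-positive rate favouring TCPM runs from 3.5% to 38% (nominal 2.5%) for incident diabetes, and the two-sided type I error from 6% to 29% (nominal 5%) for glucose change. These figures rest on invented imbalances, no true effect, complete follow-up of 300 per group and normal approximations. They show what the plan leaves possible, not what will happen.

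**What to change.** In section 2.11:
1. Make a prespecified adjusted comparison the main analysis. For FBG, 2h PBG and HbA1c, use ANCOVA or a mixed model that includes the baseline value.
2. For incident diabetes, use a time-to-event model that is propensity-score weighted or adjusted for a short covariate list, given about 110 expected events.
3. Draw covariates from what is recorded at or before allocation: age, sex, BMI, baseline glycaemia, lipids, blood pressure, TCM syndrome, concomitant medication and hospital. Table 1 schedules the measurements, syndrome differentiation is part of eligibility, and age and sex are assumed to fall under general information.
4. Keep the crude tests as a sensitivity analysis.
5. In the safety set replace randomized by enrolled, and in the full-analysis set replace postmedication by post-baseline, with both sets analysed by the group actually joined.

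In the Discussion, add self-selection and residual confounding to the limitations, with motivation as the example.

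**Cost.** Wording and slightly more analysis work, with no new visit or test. The adjusted result rests on modelling assumptions, loses some precision if group choice correlates with the covariates (factor 1.11 to 1.43 under the assumed R²), and does not remove unmeasured confounding.
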